### 3 Trial Population

#### 3.1 Inclusion Criteria

Subjects will be eligible for the study if they meet each of the following criteria:

1. Aged  $\geq 12$  years, male or female.
2. Advanced and/or metastatic GIST or other solid tumors, confirmed by histology and/or cytology. Among them, GIST patients must have primary resistance to imatinib (tumor progression within 6 months after first-line use of imatinib, or immunohistochemical presence of SDHB expression deletion or NF1 mutation) or have failed treatment with imatinib or imatinib plus at least one other TKI (following initial imatinib or other TKI treatment for more than 6 months, the subject has tumor progression again after achieving a response or stable disease).
3. ECOG score  $\leq 2$ .
4. Life expectancy of  $\geq 3$  months.
5. Hematologic function as outlined below:
  - Absolute neutrophil count (ANC)  $\geq 1.5 \times 10^9/L$  (ANC achieved by colony-stimulating factors will not be used);
  - Platelet count  $\geq 100 \times 10^9/L$  (baseline platelet count achieved by blood transfusion or thrombopoietic growth factor will not be used);
  - Hemoglobin  $\geq 90$  g/L  
Note: If hemoglobin is stable for 14 days after transfusion (a decrease of no more than 10 g/L), transfusion is allowed. The use of erythropoiesis-stimulating agents (ESAs) is allowed;
  - Serum albumin  $\geq 30.0$  g/L;
  - Serum lipase  $\leq 1.5 \times$  upper limit of normal (ULN);
  - Serum amylase  $\leq 1.5 \times$  ULN.
6. Hepatic and renal function:
  - Serum creatinine  $\leq 1.5 \times$  ULN; or serum creatinine  $> 1.5 \times$  ULN, and creatinine clearance  $\geq 50$  mL/min;
  - Serum total bilirubin  $\leq 1.5 \times$  ULN;
  - Aspartate aminotransferase (AST) and alanine aminotransferase (ALT)  $\leq 2.5 \times$  ULN ( $\leq 5 \times$  ULN in the presence of liver metastasis).
7. Cardiac function parameters:
  - Troponin (I or T)  $\leq$  ULN;

[figure not shown]

- Ejection fraction (EF)  $> 40\%$ ;
  - QTc interval on electrocardiogram (corrected by Bazett's formula): male  $\leq 450$  ms and female  $\leq 470$  ms.
8. Women of childbearing potential should have a negative serum pregnancy test within 7 days prior to the first dose of the study drug.

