### **4.3 Dose Delay and/or Dose Reduction**

#### **4.3.1 Dose interruption**

Treatment may be interrupted for up to 2 weeks (14 days) to allow study drug-related toxicity to recover to baseline or Grade  $\leq 1$ . For non-treatment-related or unexpected toxicity, whether to discontinue treatment should be decided after discussion between the investigator and the sponsor. If HQP1351 is discontinued for more than 2 weeks (14 days), the subject will be withdrawn from the study. The subject can stay in the study to receive low-dose HQP1351 treatment (determined upon discussion by the principal investigator and the sponsor) if it is considered that the subject can benefit from continuous study treatment.

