#### **4.3.2 Dose adjustment**

AEs that occur during this study will be graded according to National Cancer Institute-Common Terminology Criteria for Adverse Events (NCI-CTCAE) (v4.03). According to the correlation of AEs with the study drug and grade, the investigator will take different actions with the study drug, including maintaining the original treatment regimen, withholding dosing, reducing the dose, and terminating the treatment. Up to twice dose reductions are allowed, each to the next lower dose already explored. Any adult subject requiring a reduction of HQP1351 dose below 30 mg QOD should permanently discontinue the study treatment. The study drug can be resumed when the study drug-related toxicities resolve to grade 1 or below.

Dose adjustment may not be performed for grade 1/2 toxicities related to the study drug that can be treated by supportive treatment or don't influence normal daily activities of subjects, unless QTc prolongation, clinically significant pancreatitis, or other clinical conditions that affect subject's safety at the investigator's discretion. For intolerable (symptomatic or influencing subject's normal daily activities) or persistent (unable to be handled with the best supportive care and recovered to grade 1 or baseline after up to 2-week of drug withdrawal) grade 1/2 toxicities related to the investigational product, whether to make dose adjustment will be determined by discussion between the PI and the sponsor.

If a subject experiences grade 3 or 4 investigational drug-related toxicities, the investigational drug should be interrupted immediately. A maximum of 2 weeks (14 days) of drug interruption is permitted to resolve toxicities to Grade 1 or below, or baseline level. The investigational drug can be resumed when the toxicities resolve to Grade 1 or below, or baseline level. Each subject may undergo a maximum of twice dose reductions throughout the study period, and dose increases are generally no longer allowed after dose reductions. Please refer to Table 2-4 for guidance on dose adjustment for study drug-related toxicity.

[figure not shown]**Table 2: Dose delay and adjustment due to hematologic toxicities**

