| Grade 1                                                                                                                                                                                                                                                                                                                                                                                                                                                                                                                                                                                                                               | 
 
1. Monitor liver function once a week.
 
2. No dose adjustment is required.
 
                                                                                                                                                                                                                                                                                                                                                                                                                                                                                                           |
| Grade 2: Total bilirubin $> 1.5 \times \text{ULN}$ and $\leq 3 \times \text{ULN}$                                                                                                                                                                                                                                                                                                                                                                                                                                                                                                                                                     | 
 
1. Increase the frequency of liver function monitoring (once every 2-3 days) until it recovers to baseline level.
 
2. Dose adjustment: 
 
a) If toxicity resolves to Grade <math>\leq 1</math> within 14 days (inclusive), resume HQP1351 administration at the original dose level.
 
b) If toxicity resolves to Grade <math>\leq 1</math> beyond 14 days, or toxicity recurs, resume HQP1351 administration at a reduced dose level.
 
c) If toxicity recurs after two dose reductions, stop HQP1351 administration.
 
 
 
 |

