| Consistent with baseline grade, or increase from baseline Grade 0 to Grade 1                                                                                                                                                                                                                                                                                                                                                                                                                                                                                                                                                          | 
 
1. Monitor liver function once every 2 weeks.
 
2. No dose adjustment is required.
 
                                                                                                                                                                                                                                                                                                                                                                                                                                                                                                    |
| Grade 2 ( $>3.0$ - $5.0 \times \text{ULN}$ )                                                                                                                                                                                                                                                                                                                                                                                                                                                                                                                                                                                          | 
 
1. Increase the frequency of liver function monitoring (once every 2-3 days) until it recovers to baseline level.
 
                                                                                                                                                                                                                                                                                                                                                                                                                                                                            |

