|                                                                                                                                                                                                                                                                                                                                                                                                                                                                                                                        | 2. Dose adjustment:
a) If toxicity resolves to Grade $\leq 1$ within 14 days (inclusive), resume HQP1351 administration at the original dose level.
b) If toxicity resolves to Grade $\leq 1$ beyond 14 days, or toxicity recurs, resume HQP1351 administration at a reduced dose level.
c) Stop HQP1351 administration if toxicity recurs after two dose reductions or if toxicity resolves to baseline level beyond 14 days. |
| Grade 3 ( $>5.0 - 20.0 \times \text{ULN}$ )                                                                                                                                                                                                                                                                                                                                                                                                                                                                            | 1. Increase the frequency of liver function monitoring (once every 2-3 days) until it recovers to baseline level.
2. Dose adjustment:
a) If toxicity resolves to $\leq$ baseline level within 14 days (inclusive), resume HQP1351 administration at a reduced dose level.
b) Stop HQP1351 administration if toxicity resolves to $\leq$ baseline beyond 14 days or toxicity recurs.                                            |

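### The Grade 2 AST/ALT row of Table 3 gives both a restart and a stop instruction when baseline is regained after day 14, and Sections 4.3.1 and 4.3.2 do not settle which applies

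*Protocol*

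**What the plan says.** Table 3 of the Protocol handles a Grade 2 AST/ALT rise (above 3.0 and up to 5.0 x ULN, without bilirubin above 2 x ULN) in three items.

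- Item (a), recovery to Grade 1 or better in time: "within 14 days (inclusive), resume HQP1351 administration at the original dose level".
- Item (b), the same recovery but later: "beyond 14 days, or toxicity recurs, resume HQP1351 administration at a reduced dose level".
- Item (c): "Stop HQP1351 administration if toxicity recurs after two dose reductions or if toxicity resolves to baseline level beyond 14 days".

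The row above covers values described as "Consistent with baseline grade, or increase from baseline Grade 0 to Grade 1" and asks for no dose change. The Grade 2 bilirubin row has the same items (a) and (b), but its item (c) has only the recurrence limb: "If toxicity recurs after two dose reductions, stop HQP1351 administration".

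Two general rules sit beside the table. Section 4.3.1 says: "If HQP1351 is discontinued for more than 2 weeks (14 days), the subject will be withdrawn from the study". It then allows a subject thought to benefit to stay on a low dose after the principal investigator and the sponsor have discussed the case. Section 4.3.2 says: "Dose adjustment may not be performed for grade 1/2 toxicities related to the study drug that can be treated by supportive treatment". The same paragraph refers Grade 1/2 toxicity that is intolerable, or that persists after up to two weeks off drug, to discussion between the principal investigator and the sponsor. Section 4.3.2 presents Tables 2 to 4 as guidance.

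**The concern.** Items (b) and (c) use the same 14-day limit with two different recovery targets: Grade 1 or better in (b), baseline in (c). When reaching the second target implies the first, one clinical course satisfies a restart rule and a stop rule together. The row does not say which prevails.

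At stake is the consistency of liver-safety management. AEs leading to discontinuation are listed under Section 10.4.3, and tolerability is one of the inputs to the RP2D under Section 4.4. A contradictory stopping rule therefore touches data the trial was set up to collect, even if few subjects meet it.

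**Working it through.** The plan gives no figure to reproduce here. The check is whether the items can apply together, and to whom.

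**Inputs**
- Grade 2 AST/ALT: above 3.0 and up to 5.0 x ULN (Table 3). Grade 1 or better is therefore taken as 3.0 x ULN or less.
- Entry limit: 2.5 x ULN, or 5 x "ULN in the presence of liver metastasis" (Section 3.1).
- Time limit in items (a) to (c): 14 days. The row does not say when the count starts.

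**Step 1: does baseline imply Grade 1 or better?** Without liver metastasis, baseline is at most 2.5 x ULN. Since 2.5 < 3.0, regaining baseline always means Grade 1 or better. The same holds for any subject with liver metastasis whose baseline is 3.0 x ULN or less. A subject whose baseline is already Grade 2 (for example 4.0 x ULN) falls in the row for unchanged grade and does not reach these items while at that grade.

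**Step 2: enumerate the recovery paths.** Results are identical for baselines of 0.8, 2.0 and 2.5 x ULN.

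| Grade 1 or better reached | Baseline reached | Item (a) or (b) | Baseline limb of (c) |
|---|---|---|---|
| day 10 | day 10 | (a) restart, original dose | not met |
| day 10 | never | (a) restart, original dose | not met |
| day 10 | day 20 | (a) restart, original dose | met: stop |
| day 20 | day 20 | (b) restart, reduced dose | met: stop |
| day 20 | never | (b) restart, reduced dose | not met |

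The fourth line is the plain contradiction. Compared with the fifth, the subject who recovers fully is told to stop, while the one who never regains baseline is told only to restart. The third line is a further literal collision, but a less natural reading, because it keeps the 14-day count running after dosing has restarted.

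**Step 3: compare neighbouring rows.** The Grade 3 AST/ALT row uses baseline as the target for both its restart and its stop branch, so those branches do not overlap on recovery time. The Grade 2 bilirubin row has no baseline clause. The overlap is particular to the Grade 2 AST/ALT row.

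**Step 4: test the general rules.** In the fourth line, a subject kept off drug until day 20 has exceeded 14 days. Section 4.3.1 then says withdraw, unless a low dose is agreed. Section 4.3.2 sends persistent Grade 1/2 toxicity to discussion. Neither selects (b) or (c). Both conflict with (b) as an automatic restart, and they conflict equally with item (b) of the Grade 2 bilirubin row.

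**Step 5: size.** Among the first 36 GIST subjects (Section 1.5.2), AST increased in 0.333 x 36 = 12 and ALT increased in 0.25 x 36 = 9, all grades. The overlap is not given, so between 12 and 12 + 9 = 21 subjects had either. The Grade 2 share and the times to recovery are not given, so the number who met the contradiction cannot be derived and may be zero. For scale only, one additional AE discontinuation would move 5/36 = 13.9% (exact 95% CI 4.7 to 29.5%) to 6/36 = 16.7% (6.4 to 32.8%), and would move a group of 10 by 1/10 = 10 percentage points. This is not an estimate of the effect.

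**The case against.** The strongest reply is that the row should not be read alone. Section 4.3.1 caps interruption at 14 days, Section 4.3.2 brings the sponsor into persistent Grade 1/2 cases, and the tables are guidance. A slow recoverer off drug would normally reach sponsor discussion, which makes silent divergence between sites less likely. That stands as a limit on the consequences. It does not remove the contradiction, because neither section ranks (b) against (c), and a case-by-case rule is a third instruction beside two unconditional ones.

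A reader might infer more than the text supports:

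- **That item (c) requires a permanent stop.** The row says only to stop, although the tables do use that word separately from interrupting.
- **That a subject who stays at Grade 1 can never be stopped by (c).** Its recurrence limb can still apply, and Section 4.3.1 may lead to withdrawal.
- **That the counting of AE discontinuations is undefined.** Section 3.3 requires the reason to be recorded in the eCRF, and Section 10.4.3 lists these events. The management trigger is ambiguous; the counting is not.
- **That the RP2D is compromised.** Section 4.4 rests it on joint judgement of safety, tolerability, PK and efficacy with no discontinuation threshold. By January 2021 the 30, 40 and 50 mg groups had already enrolled 11 each, and later non-randomized adults are assigned a single dose, so scope for further distortion between doses is limited.
- **That the row is defective because it does not say to interrupt.** A restart presupposes an interruption, and Section 4.3.1 provides for one. Section 4.3.2 also lets the investigator depart from its no-adjustment rule on safety grounds.

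**Conclusion.** The point holds as an internal contradiction in a stated safety rule. For a Grade 2 AST/ALT rise in a subject entering at 2.5 x ULN or less, regaining baseline after day 14 satisfies both a restart and a stop instruction with no precedence. The collision of (c) with (a) is possible literally but secondary. Sections 4.3.1 and 4.3.2 leave the clash open and add a conflict with item (b) in both Grade 2 hepatic rows.

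This rests on two readings: Grade 1 or better means 3.0 x ULN or less, as the row's own threshold implies, and baseline means the subject's entry value. No sample size, error rate or planned estimate changes. The number of subjects affected is unknown, and the effect on discontinuation rates and the RP2D is unquantified.

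**What to change.** The sponsor should reconcile the Grade 2 AST/ALT row and the Grade 2 bilirubin row of Table 3 with Sections 4.3.1 and 4.3.2. After a Grade 2 AST/ALT rise, each path should lead to exactly one action: recovery to Grade 1 or better, recovery to baseline, each within or beyond 14 days, and recurrence. The text should also say whether the table or the general sections govern once 14 days have passed. Which action applies on each path is for the sponsor to decide.

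The cost is a short amendment to two table rows and, where needed, two paragraphs, plus a notice to sites. No additional tests are needed, because liver monitoring every 2 to 3 days is already required in these rows.

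### Protocol Table 3, AST/ALT Grade 2 row: after a late full recovery, item b) says resume at a reduced dose and item c) says stop, with no rule for choosing

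*Protocol*

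**What the plan says.** The row is in Section 4.3.2, Table 3, under AST/ALT increased without a total bilirubin rise above 2 x ULN, Grade 2 (above 3.0 up to 5.0 x ULN). It first asks for closer monitoring: "Increase the frequency of liver function monitoring (once every 2-3 days) until it recovers to baseline level". Three dosing items follow.

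- Item a), Grade 1 or below reached in time: "within 14 days (inclusive), resume HQP1351 administration at the original dose level".
- Item b), Grade 1 or below reached late: "beyond 14 days, or toxicity recurs, resume HQP1351 administration at a reduced dose level".
- Item c): "Stop HQP1351 administration if toxicity recurs after two dose reductions or if toxicity resolves to baseline level beyond 14 days".

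The bilirubin Grade 2 row of the same table has the same a) and b), but its c) contains only the recurrence rule: "If toxicity recurs after two dose reductions, stop HQP1351 administration".

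The surrounding text bears on the point in three places. Section 4.3.2 sets the general resumption threshold: "The study drug can be resumed when the study drug-related toxicities resolve to grade 1 or below". For intolerable or persistent Grade 1/2 toxicity it says "whether to make dose adjustment will be determined by discussion between the PI and the sponsor". Section 4.3.1 says "If HQP1351 is discontinued for more than 2 weeks (14 days), the subject will be withdrawn from the study", with an exception for low-dose treatment when the principal investigator and sponsor agree that the subject can benefit.

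**The concern.** Items b) and c) share the 14-day limit but use different recovery milestones, and neither yields to the other. When both milestones are first reached after day 14, one item restarts the drug and the other ends treatment. The literal result also runs the wrong way: a subject who recovers late to Grade 1 but not to baseline resumes at a reduced dose, while one who recovers equally late but completely is stopped.

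At stake is whether sites handle the same liver event alike, and whether a discontinuation for an adverse event reflects the drug or the reading of a table cell. Safety and tolerability are the primary endpoint, and Section 10.4.3 has adverse events leading to discontinuation listed in detail.

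**Working it through.** There is no figure in the plan to reproduce; this is a check of the rules against each other.

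**Who the row covers.** Inclusion criterion 6 caps AST and ALT at 2.5 x ULN, or 5 x ULN with liver metastasis. The table starts Grade 2 above 3.0 x ULN, so a subject without liver metastasis has a Grade 0 or 1 baseline. A subject with liver metastasis may start at Grade 2, but the row above requires no dose adjustment for a value at the baseline grade. The Grade 2 row therefore concerns Grade 0-1 baselines.

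**Notation.** Let T1 be the first day at Grade 1 or below and TB the first day at baseline. I count from the start of the interruption that the word resume implies. A Grade 0-1 baseline lies at or below Grade 1, so TB is never earlier than T1.

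**Conditions as written.**

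| Item | Applies when | Order |
|---|---|---|
| a) | T1 ≤ 14 | resume, original dose |
| b) | T1 > 14 (or recurrence) | resume, reduced dose |
| c), baseline clause | TB > 14 | stop |

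**Recovery courses.**

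- T1 = TB = 10: only a) applies. No conflict.
- T1 = TB = 18: b) and c) both apply. Resume at a reduced dose, and stop.
- T1 = 18, baseline not reached: only b) applies. Resume at a reduced dose.
- T1 = 10, TB = 20: a) applies on day 10; read literally, c) applies on day 20.

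If T1 > 14 and baseline is reached at all, then TB ≥ T1 > 14, so b) and c) always meet. This holds for Grade 0 and Grade 1 baselines, and whether baseline level means the measured value or the CTCAE grade.

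The last course depends more on the reading. For a Grade 0 baseline it arises on either meaning. For a Grade 1 baseline it needs the measured-value meaning; on the grade meaning TB = T1, and T1 ≤ 14 gives TB ≤ 14.

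**Dose floor.** Section 4.3.2 requires permanent discontinuation for an adult who would need less than 30 mg QOD. For an adult already at 30 mg, b) therefore also ends in discontinuation and agrees with c). The conflict is for subjects dosed above 30 mg.

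**Neighbouring rows.** In the AST/ALT Grade 3 row both items use baseline (TB ≤ 14 reduced dose, TB > 14 stop), so they cannot overlap. The bilirubin Grade 2 row has no baseline clause. Only the AST/ALT Grade 2 row mixes the two milestones.

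**Check of the repair.** Without the baseline clause, a) applies if T1 ≤ 14 and b) if T1 > 14. No course then meets both, and c) acts only on recurrence after two reductions.

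**The case against.** The strongest reply is that the main text already settles late recovery. After more than 14 days off drug, 4.3.1 makes withdrawal the default and low-dose treatment by agreement the exception. Item c) matches the default and item b) the exception; Section 4.3.2 calls the tables guidance and refers persistent Grade 1/2 toxicity to the investigator and sponsor. This stands in part: it limits the harm, because a late-recovering subject should reach that discussion anyway. It does not remove the contradiction. Item b) orders resumption without any agreement, c) orders a stop without any exception, and 4.3.1 does not rank them.

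A reader might infer that c) contradicts a) just as firmly, because a subject who resumed by day 14 and reached baseline later would then have to stop. The wording permits this, but the documents point against it. The row above requires no dose adjustment for a rise from Grade 0 to Grade 1, the general rule allows dosing at Grade 1 or below, and the 14-day limit in 4.3.1 concerns time off drug, which has ended. I treat it as secondary.

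It can also be said that the clause may have been meant to stop subjects who do not resolve, so that plain deletion would remove an intended hepatic stop. That is a fair caution, and the repair has to allow for it.

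**Conclusion.** The contradiction between b) and c) is real. It applies to subjects with a Grade 0-1 AST/ALT baseline, dosed above 30 mg, whose drug-related Grade 2 rise first reaches both Grade 1 or below and baseline after day 14. It rests on the table's own grade limits and on reading both items as live orders, since no precedence is stated.

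A reader might infer that every subject with a Grade 0-1 baseline meets conflicting orders. That is not so: a subject back at baseline by day 14 falls under a) alone.

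The size cannot be stated as a rate. Section 1.5.2 reports AST increased in 33.3% and ALT increased in 25.0% of the first 36 GIST subjects (36 x 0.333 = 12 and 36 x 0.25 = 9). Those figures are not limited to Grade 2, drug-related events with late recovery, so they show only that liver enzyme rises are common here. No sample size, error rate or efficacy definition is affected. The row should be corrected because a hepatic dosing rule ought to give one order; the point does not threaten the trial's conclusions.

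**What to change.** 1. In item c) of the AST/ALT Grade 2 row, delete the second condition, on return to baseline level after day 14. Use Grade 1 or below as the only milestone in the row's dosing items.
2. Reword item b): *If toxicity recurs, resume at a reduced dose level. If Grade 1 or below is not reached within 14 days, follow 4.3.1: withdraw, unless the principal investigator and sponsor agree the subject can benefit, in which case resume at a reduced dose level once Grade 1 or below is reached (adults not below 30 mg QOD).*
3. Give item b) of the bilirubin Grade 2 row the same wording, since it has the same text now.
4. Leave item a) and the Grade 3 rows unchanged.

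Because withdrawal stays the default after day 14, this keeps a hepatic stop even if the deleted clause was meant to cover toxicity that does not resolve. The cost is an edit to two rows of Table 3, with no new visits, tests or data. The downside is that a few late-recovering subjects may be re-exposed at a lower dose with sponsor agreement; liver tests every 2-3 days until baseline and the stop on recurrence after two reductions remain.

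### Table 3, Grade 2 AST/ALT: item (c) stops a subject who returns to baseline after Day 14, while item (a) or (b) tells the same subject to resume

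*Protocol*

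**What the plan says.** Table 3 sets the hepatic dosing rules. For Grade 2 AST/ALT (above 3.0 and up to 5.0 x ULN, without bilirubin above 2 x ULN) it has three dosing items:

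- (a) Grade 1 or below reached within 14 days: resume at the original dose.
- (b) Grade 1 or below reached later, or recurrence: "beyond 14 days, or toxicity recurs, resume HQP1351 administration at a reduced dose level".
- (c) A stop rule with two limbs, one on recurrence and one on late return to baseline: "Stop HQP1351 administration if toxicity recurs after two dose reductions or if toxicity resolves to baseline level beyond 14 days".

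The row above it needs no dose adjustment and covers values described as "Consistent with baseline grade, or increase from baseline Grade 0 to Grade 1".

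The Grade 2 bilirubin row in the same table has matching items (a) and (b). Its stop item contains only the recurrence limb: "If toxicity recurs after two dose reductions, stop HQP1351 administration".

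The general text also bears on late recovery. Section 4.3.1 states: "If HQP1351 is discontinued for more than 2 weeks (14 days), the subject will be withdrawn from the study". It then allows continuation at a low dose if benefit is expected and the principal investigator and sponsor have discussed it. Section 4.3.2 says of intolerable or persistent Grade 1/2 drug-related toxicity that "whether to make dose adjustment will be determined by discussion between the PI and the sponsor". It refers to Tables 2-4 as guidance and does not say which text prevails.

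**The concern.** Items (a) and (b) measure recovery against Grade 1 or below. The second limb of item (c) measures it against the subject's own baseline and orders a stop when baseline is reached late. Where baseline lies within Grade 0-1, these conditions overlap and the actions are opposite. The direction is also odd: the stop is triggered by full recovery, not by failure to recover.

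Sites apply this hepatotoxicity rule directly, and it is not something a statistical analysis plan would settle. Two sites could handle the same recovering subject differently. One subject could lose treatment after full recovery, or be restarted where a stop was meant. The trial's primary purpose is safety and tolerability, and section 10.4.3 lists AEs leading to discontinuation in detail.

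**Working it through.** No figure in the plan depends on this rule, so the check is to lay the items side by side.

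**Who is in the row.** Values consistent with the baseline grade fall in the no-adjustment row. A subject with Grade 2 at baseline (possible only with liver metastasis, where inclusion criterion 6 allows up to 5 x ULN) therefore does not enter the Grade 2 row on a Grade 2 value. In practice the row covers baseline Grade 0 or 1.

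**Consequence.** For these subjects, being at baseline implies being at Grade 1 or below. Baseline therefore cannot be reached before Grade 1 or below is reached.

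**Conditions, first episode, no earlier reduction.** Let G be the day Grade 1 or below is first reached and B the day baseline is reached, with B no earlier than G.

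- (a) applies if G is at most 14.
- (b) applies if G is above 14.
- (c), second limb, applies if B is above 14.

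| G | B | Items met | Instructions |
|---|---|---|---|
| 10 | 10 | (a) | resume, original dose |
| 10 | 18 or 22 | (a) and (c) | resume, original dose; stop |
| 18 | 18 or 22 | (b) and (c) | resume, reduced dose; stop |
| 18 | not reached | (b) | resume, reduced dose |

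The result is the same for baseline Grade 0 and Grade 1. Every subject with B above 14 has G either at most 14 or above 14, so (c) always collides with (a) or (b). In the second line of the table, a subject already restarted on Day 10 meets the stop condition on Day 18 by completing recovery. The third and fourth lines show the inversion: same G, but only the subject who goes on to baseline is told to stop.

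**Does other text resolve it?**

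- Section 4.3.1 makes withdrawal the default after more than 14 days off drug, with a low-dose exception after discussion. The exception could support (b) and the default could support (c), but neither cancels the other item. It does not reach the (a)/(c) case, where drug was resumed by Day 14.
- Section 4.3.2 sends persistent Grade 1/2 toxicity to discussion, whereas (a), (b) and (c) are unconditional.
- The Grade 2 bilirubin row does without the baseline limb, so the limb is not needed for the ladder to work.

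**The case against.** The best defence is that item (c) was meant differently. The two-reductions condition might govern both limbs, giving an ordered ladder of original dose, reduced dose, stop. That would remove the first-episode clash. But the second limb opens with its own condition, and nothing in the text carries the reductions over to it. Alternatively, (c) may have meant failure to reach baseline by Day 14. That does not help: a subject who first reaches Grade 1 or below after Day 14 has necessarily not reached baseline by Day 14, so (c) would void the late-recovery limb of (b). A subject at Grade 1 above baseline on Day 14 would still meet both (a) and (c).

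A second defence stands in part. Stop and withdrawal mean the same for the drug, so the real dispute is restart against stop, and both general rules bring in the principal investigator and sponsor. That is a partial safeguard and limits the harm.

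A reader might infer three stronger points that the document does not support:

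- **That the Grade 3 AST/ALT row also contradicts 4.3.2.** It requires "baseline level within 14 days (inclusive), resume HQP1351 administration at a reduced dose level", whereas 4.3.2 allows restart at Grade 1 or below, or at baseline. But 4.3.2 is permissive about restart and refers to the tables, so a stricter hepatic row breaches nothing. Other rows also set their own thresholds (neutrophils, anemia). A subject not back at baseline by Day 14 falls under the 4.3.1 default.
- **That the clash shifts a trial result by a known amount.** One subject over the sample size describes any single subject in any trial. The primary endpoint lists name neither dose reductions nor a discontinuation rate.
- **That one sentence giving Tables 2-4 precedence would cure it.** It would not remove a clash inside one table row, and it would do harm. Section 4.3.2 stops adults who would need less than 30 mg QOD, so an adult on 40 mg has one step left. The tables allow two reductions and 20 mg has been explored, so an override would put that floor in doubt. It would also remove the 4.3.1 discussion for late Grade 2 bilirubin recovery.

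**Conclusion.** The Grade 2 AST/ALT row is contradictory as written. For a subject with baseline Grade 0-1 who reaches baseline only after Day 14, item (c) orders a stop, while (b) orders a reduced-dose restart or (a) an original-dose restart, depending on whether Grade 1 or below was first reached after or by Day 14. Full recovery by Day 14 is unaffected.

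The number of subjects concerned cannot be estimated. Section 1.5.2 reports AST increased in 33.3% and ALT increased in 25.0% of 36 GIST subjects, without a split by grade or recovery time. No sample size, error rate or planned estimate is affected.

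The conclusion rests on a literal reading of the row and on the no-adjustment row keeping baseline Grade 2 subjects out of it. The point should be corrected because it is an operative safety rule and the correction is cheap.

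**What to change.** Delete the baseline limb of item (c) and make the Grade 2 AST/ALT items non-overlapping and consistent with 4.3.1:

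- (a) Grade 1 or below by Day 14: resume at the original dose.
- (b) Not at Grade 1 or below by Day 14: stop, unless the principal investigator and sponsor agree to resume at a reduced dose once Grade 1 or below is reached.
- (c) Recurrence: resume at a reduced dose (adults not below 30 mg QOD, as in 4.3.2). Recurrence after two dose reductions: stop.

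The Grade 2 bilirubin row also restarts automatically after Day 14, in tension with 4.3.1. Put the same principal investigator and sponsor gate on late recovery there, so that the parallel rows agree. Do not add a general sentence that Tables 2-4 override 4.3.1 and 4.3.2, and leave the Grade 3 row as it is.

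The cost is a wording amendment to two rows of Table 3. It needs no additional subjects, visits or procedures.
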